### Outcome measures (Table 4, Fig. 5)

**Table 4 Tab4:** Outcome measures

Characteristics & confounders	Description and instrument	Data source	Sample	Collection points
Patient’s characteristics	Date of birth, gender, ethnicity, BMI (height, weight), site (s) of OA diagnosis, date of first OA diagnosis, labour situation (working, retired, unemployed, in rehabilitation status)	SAQ, IDB	IG, CO	t0, t3, t6, t12, t24
Primary outcome measure	Clinical Outcomes			
Pain	WOMAC Index 3.1 German (11-box NRS): subscale pain	SAQ	IG, CO	t0, t3
Function	WOMAC Index 3.1 German (11-box NRS): subscale physical functioning	SAQ	IG, CO	t0, t3
Secondary outcome measures	Clinical Outcomes		IG, CO	
Stiffness, disease specific impairment	WOMAC Index 3.1 German (11-box NRS): subscale stiffness, overall score	SAQ	IG, CO	t0, t3, t6, t12, t24
Pain, physical function	WOMAC Index 3.1 German (11-box NRS): subscale pain, subscale physical function	SAQ	IG, CO	t6, t12, t24
Health related quality of life	VR-12 incl. VR-6D utility index (4-week-time-slot)	SAQ	IG, CO	t0, t3, t6, t12, t24
General Self-Efficacy	General self-efficacy scale (GSE)	SAQ	IG, CO	t0, t3, t6, t12, t24
Response to exercise	Omeract-OARSI Set of Responder Criteria: composite score with minimum absolute and relative change levels for pain or pain & function	SAQ	IG, CO	t0, t3, t6, t12, t24
Physical activity status	Habitual physical and sports activity status	SAQ	IG, CO	t0, t3, t6, t12, t24
Time to surgery	Endpoint “elective joint replacement”	IDB	IG, CO	t0, t3, t6, t12, t24
	Patient satisfaction			
	Modified version of the ZUF-8 Questionnaire to assess patient satisfaction	SAQ	IG	t3
	Economic data			
Unspecific and specific (OA-related) health care costs	Out-patient costs, hospital costs, costs related to drugs, adjuvants and physical modalities, rehabilitation costs, sick-pay	IDB	IG, CO	tm24, tm18, tm12, tm6 t0, t3, t6, t12, t24
Unspecific/specific (OA related) periods of disability	Days of disability (overall and related to OA)	IDB	IG, CO	tm24, tm18, tm12, tm6 t0, t3, t6, t12, t24
Intervention related costs	Costs for human and physical resources/session	IDB	IG	t3, t6, t12, t24
	Adherence to exercise			
Training adherence	Summarized number of attended training sessions according to training log	SAQ	IG	t3
	Safety evaluation			
Adverse events and side-effects	Summarized number and details of adverse events and side-effects according to training log	SAQ	IG	t3

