#### Matching procedures and statistical analysis of clinical endpoints

The matching procedure for the statistical twins of the control group (CO) will be conducted as followed: ten statistical controls for each participant of the intervention group will be selected from the insurance data base according to the matching criteria displayed in Table 5. If it is not possible to select ten matches for a subject of the intervention group according to the criteria and tolerances displayed in Table 5, the tolerance will be extended in an iterative manner (steps of 100 Euro or 1 day respectively) until ten controls can be extracted from the data base.

**Table 5 Tab5:** Matching criteria to extract 10 controls for each participant of the intervention

Criteria	Tolerance
Co-morbidity: Quantity of hierarchical ordered morbidity groups in the previous year	0
Osteoarthritis of the hip or knee joint in the previous year: yes/no	0
Participation in a special general practitioner care program (“Hausarztzentrierte Versorgung”): yes/no	0
Routine data: Age (years), gender, type of insurance (compulsorily insured, family insured, pensioner, unemployed), complexity of work (from 1 = low to 4 = high), level of education (1 = no graduation to 4 = High School), highest level of educational attainment (from 1 = no qualification to 6 = doctoral degree), contractual form (permanent/fixed term contract, full time/part time)	0
Joint replacement in the last 24 month prior t0 at the hip and/or knee joint(s): yes/no	0
Sum of unspecific health care costs (overall costs) in the last 24 month prior t0: Sick-pay, hospital costs, out-patient costs, costs related to periods of disability and costs related to drugs, physical modalities and adjuvants.	+/− 100 EUR
Sum of unspecific health care costs (overall costs) in the last 6 month prior t0 (tm6): Sick-pay, hospital costs, out-patient costs, costs related to periods of disability and costs related to drugs, physical modalities and adjuvants.	+/− 100 EUR
Sum of specific diagnosis (hip/knee OA) related health care costs in the last 24 month prior t0: Sick-pay, hospital costs, out-patient costs, costs related to periods of disability and costs related to disease related drugs, physical modalities and adjuvants such as walkers, cranks or orthotics.	+/− 100 EUR

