Sum of specific diagnosis (hip/knee OA) related health care costs in the last 6 month prior t0 (tm6): Sick-pay, hospital costs, out-patient costs, costs related to periods of disability and costs related to disease related drugs, physical modalities and adjuvants such as walkers, cranks or orthotics.	+/− 100 EUR
Disability days in the last 24 month prior t0 (tm24)	+/− 1 Day
Disability days in the last 6 month prior t0 (tm6)	+/− 1 Day
Specific disability days (hip/knee OA) days in the last 24 month prior t0 (tm24)	+/− 1 Day
Specific disability days (hip/knee OA) in the last 6 month prior t0 (tm6)	+/− 1 Day

Legend: a tolerance of “0” is equal to complete agreement, i.e. for age in years. Matching criteria are derived from the insurance data base

The matching process for the identification of statistical controls (CO) for each subject of the intervention group will be permuted in blocks: The matching procedure will be conducted quarterly until the number of needed subjects is reached.

Selected subjects will be asked for study participation (see section recruiting). The final statistical twins for each participant (1:1 matching) will be selected from all eligible responders. As a primary criterion, twins must be identical with regard to site(s) of OA (hip, knee or both). The following independent variables of the self-administered questionnaires (SAQ) and insurance data base (IDB) will then be used as input variables for the logistic regression of the PSM:Socio-demographic data at t0: age and gender (SAQ)Co-morbidity: Quantity of hierarchical ordered morbidity groups in the previous year (IDB)Osteoarthritis of the hip or knee in the previous year (IDB)WOMAC Index subscale pain at t0 (SAQ).WOMAC Index subscale physical functioning at t0 (SAQ).Quality Adjusted Life Years at t0 via VR-6D (SAQ).Body mass index at t0 (SAQ).Joint replacement hip and/or knee joint(s) at t0 (SAQ).General Self-Efficacy scale GSE at t0 (SAQ)Habitual physical and sports activity status at t0Participation in health activity programs (i.e. walking courses) at t0

If there are any cost/disability day categories, in which the standard mean differences after matching are above 0.05, a new matching will be conducted with these cost/disability day categories as matching variables in addition. No follow-up data will be analyzed prior to the final definition of the statistical twin of the CO for a given IG patient.

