#### Economic evaluation

Cost-efficiency of the intervention will be quantified on the expanded perspective of the payer. If a dominant strategy doesn’t exist (i.e.: lower costs and higher health related effects in the intervention group), the costs will be related to the effects. The costs (including the supplementary costs of the pilot offer for participants) will be related to the differences between the groups (Double-Difference Method, two years pre and two years post intervention) in Quality Adjusted Life Years (QALYs, equation 1) and health related effects (WOMAC Index: equation 2). The costs of the intervention will further be related to the differences in costs (Double-Difference Method of the health care costs (unspecific health care costs (overall costs), specific health care costs and the costs for days of disability (human capital approach): equation 3). The time to surgery will be estimated using the Kaplan-Meier method. For the economic evaluation all participants have to be members of the insurance the period from 24 months before baseline (tm24) up to 24 month after baseline (t24).

Equation 1: Cost-Utility Analysis (CUA) = Incremental Cost Utility Ratio (ICUR)$$ ICUR\kern0.49em =\kern0.49em \frac{\varDelta\ \mathrm{Cost}}{\varDelta\ \mathrm{QALYs}} $$

Equation 2: Cost-Effectiveness Analysis (CEA) = Incremental Cost-Effectiveness Ratio$$ ICER\kern0.49em =\kern0.49em \frac{\varDelta\ \mathrm{Cost}}{\varDelta\ \mathrm{Effect}} $$

Equation 3: Cost-Benefit Analysis (CBA) = Incremental Cost-Benefit-Ratio$$ ICBR\kern0.49em =\kern0.49em \frac{\varDelta\ \mathrm{Cost}}{\varDelta\ \mathrm{Benefit}} $$

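### The final 1:1 match leaves out work status, so part of a group difference in disability days or sick-pay may only reflect a different share of people in work

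*Protocol article*

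**What the plan says.** Table 4 lists "Days of disability (overall and related to OA" and sick-pay as insurance-database outcomes in both groups, with no restriction to people in work. Under Economic evaluation, days of disability are valued as a cost, in the plan's words "specific health care costs and the costs for days of disability (human capital approach", and enter Equation 3. The contrast is the "Double-Difference Method, two years pre and two years post intervention". The only population rule given there is membership: "For the economic evaluation all participants have to be members of the insurance the period from 24 months before baseline" to 24 months after it.

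Controls are chosen in two stages:

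- **Pool, ten per participant (Table 5).** Exact agreement is required on, among others, age, "type of insurance (compulsorily insured, family insured, pensioner, unemployed" and "contractual form (permanent/fixed term contract, full time/part time". Past costs and past disability days must agree within a tolerance, which may be widened.
- **Final twins, one per participant (Matching procedures).** These come from the responders as a whole, not from each participant's own ten. Exact agreement is required on the site of osteoarthritis only. The socio-demographic part of the propensity score reads "Socio-demographic data at t0: age and gender (SAQ". Any cost or disability-day category with a standardised mean difference above 0.05 after matching triggers a new match that adds the category.

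Table 4 also records "labour situation (working, retired, unemployed, in rehabilitation status" from questionnaire and database at baseline and at every follow-up. It is not among the inputs to the final match.

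**The concern.** Pricing lost days by the human capital approach treats them as lost work. The insured population expressly includes pensioners and family-insured members. If such people record few or no disability days whatever their joint symptoms, the mean per participant depends on how many in each group are in work.

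The plan treats type of insurance and contractual form as important enough for exact agreement in the pool, then does not carry them into the final match. Controls who answer the mailing may differ in work status from those who do not, and twins are re-paired across all responders, so the agreement need not survive. A difference in disability days, in sick-pay or in the benefit term of Equation 3 could then partly reflect who is in the groups. The Discussion expects much smaller effects for economic than for clinical outcomes, so a shift of a day or two per participant could matter.

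**Working it through.** The plan gives no share of workers and no mean or spread of disability days, so there is no figure of its own to reproduce here. Its sample size of 278 per group concerns the WOMAC endpoints and does not bear on this point.

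**From the protocol:** the 0.05 limit; 24 months before and after baseline; a 60 % response among controls in the insurer's earlier back-pain study.

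**Assumed:** people not in work record zero days; share working p = 30 to 70 %; workers' mean m = 20 to 40 days per 24 months; workers' SD s two or three times m; correlation r = 0.3 to 0.6 between a worker's days before and after baseline.

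**1. How a gap can arise.** Invited controls agree with the intervention group on type of insurance. If workers respond at rate a and others at rate b, the share working among responders is p·a / (p·a + (1 − p)·b).

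- p = 0.5, a = 0.55, b = 0.65: 0.275/0.600 = 45.8 %, a gap of 4.2 points.
- p = 0.5, a = 0.50, b = 0.70: 0.250/0.600 = 41.7 %, a gap of 8.3 points.

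Over p = 0.3 to 0.7 these two patterns give about 3 to 8 points before the propensity match. Age is in that match and will remove some of the gap.

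**2. What the 0.05 rule lets through.** A gap d shifts mean past days by d·m. With CV = s/m, the SD over all participants is m·√(p(CV² + 1) − p²), so the largest gap that passes is 0.05·√(p(CV² + 1) − p²).

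- p = 0.3, CV = 2: 0.05·√1.41 = 5.9 points.
- p = 0.7, CV = 3: 0.05·√6.51 = 12.8 points.
- At p = 0.5, a 10-point gap passes only if 0.5·CV² + 0.25 ≥ 4, that is CV above about 2.7. A 5-point gap passes if 0.5·CV² + 0.25 ≥ 1, that is CV above about 1.2.

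The rule limits the gap but can let several points through.

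**3. Double difference, gap also present before baseline.** The bias is d × (workers' mean after − workers' mean before). With m = 40 it is 0 if the mean is unchanged. If the mean changes by 25 %, it is 0.05 × 10 = 0.5 day or 0.10 × 10 = 1.0 day.

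**4. Double difference, past days equalised by re-matching but work status not.** Let one group have share p + d and the other p. Equal past means require the first group's workers to average m·p/(p + d), which is m·d/(p + d) below m. Under linear regression to the mean with equal variances, a fraction r of that shortfall remains afterwards. The later difference is (p + d)·[m − r·m·d/(p + d)] − p·m = (1 − r)·d·m, and no earlier difference is left to subtract.

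- d = 0.10, m = 40: 0.4 × 4 = 1.6 to 0.7 × 4 = 2.8 days.
- d = 0.05, m = 40: 0.4 × 2 = 0.8 to 0.7 × 2 = 1.4 days.

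Check with p = 0.5, d = 0.10, r = 0.6: the workers' past mean is 40 × 0.5/0.6 = 33.3, their later mean is 40 − 0.6 × 6.67 = 36, and 0.6 × 36 − 0.5 × 40 = 1.6. This is the unfavourable end. Under the zero-days assumption anyone with past days is in work, so re-matching on days would also draw the work shares somewhat closer.

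**5. Disability days as a secondary outcome.** The Statistics section says secondary endpoints are analysed like the primary ones, by a linear model with the propensity score as covariate. It does not tie disability days to the double difference. Without differencing, a gap left in place shifts the mean by d·m, which is 2 to 4 days for 5 to 10 points at m = 40.

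**The case against.** A reader might infer that any difference in the share of workers becomes an effect on disability cost, at gap times mean days. The documents do not support that. Costs are analysed by a double difference, and a stable gap visible in both periods cancels. The pool is matched exactly on age, gender, type of insurance and contractual form, age and gender enter the final score again, and the 0.05 rule works on group means, where a large gap would usually show in past days. The protocol gives no figure that points to a gap of 5 or 10 points. The 0.05 limit is also set for cost and disability-day categories, so a gap in work status cannot be said to breach it. All of this stands and reduces the size.

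A second tempting inference is that retirement during follow-up biases the contrast. Age is matched, so that loss should be much the same in both groups and would largely cancel.

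A third is that averaging over people not in work is wrong. For cost per insured person, a pensioner's zero is a true zero, and the plan takes a payer perspective. The all-participant mean is the right quantity for that purpose. An analysis confined to workers answers a different question.

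Finally, these outcomes are secondary and not confirmatory, and no passage says that only people in work record disability days or sick-pay. The last point is an inference from the costing method, stronger for pensioners and family-insured members than for the unemployed.

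None of this explains why work status is dropped at the final stage. The two safeguards also do not simply add up: the rule may remove the very pre-baseline gap that the double difference would need in order to subtract it.

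**Conclusion.** The point holds in limited form. The final match does not protect agreement on work status, and outcomes that probably depend on it are analysed in everyone. The size is unknown. For a gap of 5 to 10 points and 40 days per worker over 24 months, the residual bias in the double difference runs from 0 to 2.8 days per participant, in either direction. It rests on the assumptions that people not in work record no days, that response or re-pairing opens such a gap, and that r lies between 0.3 and 0.6 where past days have been equalised. If the shares in work turn out equal, this source of bias is absent. The primary WOMAC comparison is not touched by this argument. It is an inexpensive improvement to the secondary economic outcomes and does not invalidate the economic evaluation.

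**What to change.** In item (5) of the control-group selection and in the list of propensity inputs, add labour situation at baseline (or type of insurance), either as an input or as an exact criterion beside the site of osteoarthritis. Report its standardised difference in the post-matching balance check together with the cost and disability-day categories. State whether disability days as a secondary outcome are analysed by double difference.

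Keep the all-participant mean for payer cost. Add a supportive analysis of disability days and sick-pay in those working at baseline, fixing beforehand how unemployed people and those in rehabilitation are classed. That analysis does not deal with people who leave work later, but labour situation is recorded at each follow-up, so rates of leaving work can be described by group.

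The cost is wording, since the variable is already collected in both groups. The price is one more matching variable with slightly fewer close matches, and a smaller sample for the supportive analysis.

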## Methods/design

### Design (Fig. 1)

**Fig. 1 Fig1:**
[figure not shown]
Study flow chart

This is a multi-center non-randomized controlled trial of an 11-week hip and knee training (HKT) with a 24 months follow-up period in the context of health services research. The exercise intervention comprises 8 supervised group sessions (1× / week for 8 weeks) and a home exercise program (2× / week for 11 weeks). All participants are insurance holders of a large statutory health insurance company covering approx. 40 % of the total population of the state Baden-Wuerttemberg. Participants of the intervention group (IG) will be compared to “statistical twins” (matched pairs) to investigate the effects of an exercise intervention on clinical and economic outcomes. Measurements will be taken at baseline (t0), 3 months (t3), 6 months (t6), 12 months (t12) and 24 months (t24). Economic data will further be evaluated retrospectively for two years prior to baseline.Recruitment of the intervention group (IG)IG is recruited out of eligible participants of a countrywide health care offer of the above mentioned insurance company. Prerequisites for exercise participation are (1) membership in the insurance company, (2) referral from an orthopaedic surgeon or general practitioner because of complaints at the hip and/or knee. To be included into the accompanying study, exercise participants further have to confirm a self-reported lifetime prevalence of hip and/or knee OA. They have to affirm the following two questions according to the German Federal State health reporting system criteria [2]:1. “Have you ever visited a doctor because of complaints in the hip and/or knee joint?”2. “If yes, did a medical doctor ever ascertain OA or a degenerative disorder at your knee and/or hip joint?”Further inclusion- and exclusion criteria for study participation are listed in Table 1.

**Table 1 Tab1:** Inclusion and exclusion criteria for study participation (t0 = baseline)

Inclusion criteria (all criteria relevant for study eligibility)
• Insurance holder of the insurance company offering the exercise program since two or more years prior t0
• Referral from an orthopaedic surgeon or general practitioner
• Self-reported lifetime prevalence of hip and/or knee OA that was previously diagnosed by a medical practitioner • Physical and mental ability to participate in the interventional program and to answer self-administered questionnaires at t0

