
### Statistics

#### Sample size

Below are given details on the sample size estimation for primary clinical outcomes. However, aside from statistical power, a sufficiently large sample is necessary to obtain representative results for the general population and to allow sustainable statements on the effectiveness and efficiency of the intervention for secondary clinical as well as economic outcomes. We therefore plan to include all eligible patients willing to participate in the study and finally assume a number of n = 700 in each group. This number takes into consideration the degree of capacity utilization of hip and knee training courses as well as the number of subjects non eligible due to inclusion- and exclusion criteria as well as subjects refusing consent to participate in the study (Fig. 1).

The empirical basis of the sample size estimation for primary outcomes was retrieved from the paper by Krauss et al. [17]. In this randomized controlled trial (RCT), intra-individual differences of WOMAC subscale pain and WOMAC subscale physical function identically showed an effect size of about 0.5 between the intervention and the control group (pain, intervention: −8.5 ± 13.9, control: −1.3 ± 15.3, physical function, intervention: −8.4 ± 13.4, control: −2.1 ± 12.9).

Based on the previous results of the RCT and the so-called efficacy-effectiveness gap between RCTs and studies under real life conditions [32] we finally assume an effect size of ES = 0.3.

Due to the fact that we want to test the two endpoints (pain and physical function) simultaneously and without hierarchical order, we choose a level of significance of 0.025 (two-sided, Bonferroni correction) and a power of 0.90. This leads to a sample size of 278 subjects per group in the parallel group design without cluster effects (nquery release 7.0). The drop-out rate in the intervention group of the above mentioned RCT was 8 % [17]. As this value is quite low, we assume a somewhat higher number of non-finishers and estimate the rate to be 20 %. Thus 350 subjects should be allocated to each treatment arm.

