The finally defined controls and cases will be included into a linear model with the propensity score as covariate. Additionally, we will use models for longitudinal data using each measurement point (instead of only t0 and t3 for the primary analysis). The level of significance will be 0.025 for primary endpoints. Secondary endpoints will be analyzed analogously without claiming confirmatory interpretation of *p*-values.

Descriptive analysis will include absolute and percentage frequencies for categorical variables, means, medians, standard deviations, quartiles and ranges for quantitative variables and medians, quartiles and ranges for ordinal variables. For the main results, two-sided 95 % confidence limits will be given additionally to significance tests. For percentages exact confidence interval for proportions based on the binomial distribution will be given.

Exploratory, prognostic factors will be analyzed using multiple regression models (linear regression) to identify potential responders to the training.

Correlation analyses will use Pearson product moment correlation coefficient (normally distributed variables) and Spearman correlation (non-normally distributed variables).

The primary analysis will be done on the full set of patients recruited in consideration of the exclusion criteria “limited pain and impairment in physical function” (WOMAC Index subscales pain and physical function with values below 15) except for patients refusing consent during the study and obviously wrongly diagnosed patients. A secondary analysis will be done using the full set of eligible and included patients irrespective of their limitations in pain and physical function at baseline (t0). This secondary analysis will only claim confirmatory interpretation of p-values if the primary analysis is able to detect group differences in a statistical manner. Otherwise the secondary analysis will be done in an explorative manner.

Missing values will be imputed using multiple imputation approaches, complete case and last observation forward analysis will be performed as a sensitivity analysis. No interim analysis, except for administrative purposes will be performed. All statistical analysis will be done using the software SPSS and R in the newest release.

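### The economic evaluation is limited to participants still insured at month 24, so its cost and QALY results leave out anyone who dies or changes insurer during follow-up

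*Protocol article*

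**What the plan says.** All references are to the protocol article.

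- **Economic evaluation.** For this evaluation, "all participants have to be members of the insurance the period from 24 months before baseline (tm24) up to 24 month after baseline". Group differences in QALYs and WOMAC, to which costs are related, come from a "Double-Difference Method, two years pre and two years post intervention" comparison. The sentence just before the membership rule reads: "The time to surgery will be estimated using the Kaplan-Meier method".
- **Table 1 (entry criteria).** "Insurance holder of the insurance company offering the exercise program since two or more years prior t0". No criterion there concerns membership after baseline.
- **Table 4 (outcomes).** Costs and disability days come from the insurance data base. WOMAC and the VR-6D utility come from postal questionnaires. Time to surgery (endpoint "elective joint replacement") is listed among the clinical outcomes, apart from the economic block, although its source is also the insurance data base.
- **Matching procedures and statistical analysis of clinical endpoints.** "The final statistical twins for each participant (1:1 matching) will be selected from all eligible responders". For missing data: "Missing values will be imputed using multiple imputation approaches", with complete-case and last-observation-carried-forward analyses as sensitivity checks.
- **Sample size.** The authors "finally assume a number of n = 700 in each group".

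The Economic evaluation section states no handling of death or change of insurer, and no analysis without the restriction.

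**The concern.** Whether someone meets the second half of the rule is known only at t24, so the economic population is defined by something that happens after baseline. One of those events, death, is itself part of the outcome: it ends cost accrual, is often preceded by high cost, and sets later utility to zero. Removing the deceased deletes outcome data instead of leaving them missing. People who change insurer lose all their data too, including costs recorded before they left.

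The groups are not randomized. The intervention group signed up for the insurer's own course on a physician's prescription; controls were approached by letter. Equal rates of death or switching cannot be taken for granted. The Discussion calls cost-utility a special interest of the study and gives power for the economic evaluation as the reason for enrolling everyone eligible, so this is not a marginal analysis.

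**Working it through.** The article gives no sample size, exit rate or mortality figure for the economic evaluation, so there is no stated result to reproduce. The check is a reading of the rule, followed by illustrations. Every rate, utility and cost below is an assumption; only the 700 per arm comes from the article.

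**1. What the rule adds.** It spans tm24 to t24, that is 24 months before and 24 months after baseline. Table 1 already secures the first 24. The only new restriction is continuous membership from t0 to t24. The article does not mention death, but a deceased person is not a member up to t24 and so fails the rule.

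**2. Does another rule bring these people back?** The imputation rule is stated under clinical endpoints. Imputation fills in values for people in the analysis set; it does not restore people whom the population definition has removed.

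**3. Number removed per arm** = 700 × exit proportion by t24.
- 2%: 700 × 0.02 = 14
- 5%: 700 × 0.05 = 35
- 10%: 700 × 0.10 = 70

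**4. QALYs over 24 months.** Assume utility 0.70 while alive, the same in both groups, and deaths at 12 months on average. With mortality d, the mean QALY is 0.70 × 2 × (1 − d) + 0.70 × 1 × d = 1.40 − 0.70d. The group difference from mortality is therefore 0.70 × (d control − d intervention).
- 2% v 2%: 0.70 × 0 = 0
- 3% v 2%: 0.70 × 0.01 = 0.007
- 4% v 2%: 0.70 × 0.02 = 0.014

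The restricted set shows 0 in all three cases. For scale, an assumed utility gain of 0.01–0.02 held for two years is worth 0.02–0.04 QALY.

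**5. Costs over 24 months.** Assume 6,000 EUR for those who stay and 10,000–30,000 EUR for those removed. The full-set mean is 6,000 + (cost of removed − 6,000) × proportion removed.
- 2% in both groups: each mean is understated by 4,000 × 0.02 = 80 to 24,000 × 0.02 = 480 EUR; the difference is unaffected.
- 3% control v 2% intervention: intervention minus control is −40 to −240 EUR in the full set, 0 in the restricted set.
- 4% v 2%: −80 to −480 EUR in the full set, 0 in the restricted set.

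**6. Time to surgery, if the rule were applied to it.** Simulation with a 24-month surgery risk near 8%:

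| Assumption | True risk | Kaplan-Meier, censoring at exit | Restricted set |
|---|---|---|---|
| Exit unrelated to surgery risk | 0.080 | 0.080 | 0.080 |
| Shared frailty, about 5% exit | 0.0755 | 0.073 | 0.071 |
| Shared frailty, about 9% exit | 0.0754 | 0.071 | 0.067 |

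Restriction does no harm when exit is unrelated to surgery. When the two are related, censoring is also biased, but less than restriction.

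**The case against.** Four arguments on the other side carry weight.

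*The bias may be nil.* Candidate controls agree exactly with intervention participants on age, gender and number of morbidity groups, and serious limiting co-morbidity is an exclusion. If exit and its link to outcome are the same in both groups, the between-group difference is unbiased. This stands, and is why the ranges above start at zero. A reader might assume a large mortality gap, but nothing in the article supports one.

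*Counting deaths could mislead.* Without randomization, a mortality gap may reflect healthier people choosing the course. Scoring deaths as zero utility would then credit residual confounding to an 11-week program. This stands as a reason to report both analyses, not as a reason to show only the restricted one.

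*The data may not exist.* Insurance cost records presumably stop when someone changes insurer, which makes the rule a complete-case choice. That is fair for leavers after exit. It does not explain dropping the deceased, or leavers' costs before exit.

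*The outcomes are secondary.* The primary WOMAC comparison at t3 is untouched, and secondary endpoints are not given confirmatory interpretation. This limits the severity.

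Three stronger readings are tempting but not supported. First, a reader might infer that time to surgery falls under the rule, because the Kaplan-Meier sentence precedes it. The rule is worded for the economic evaluation, and Table 4 and the study aims treat time to surgery separately from economic data. Second, a reader might infer that Kaplan-Meier would be left with nothing to do. Even under the rule, people who withdraw consent could still need censoring, and without any censoring the method remains valid as the empirical curve. Third, a reader might infer that matching is undone because one twin can be lost. The Sample size section rejects a matched-pair analysis, so a lost twin is not in itself a defect; group balance suffers only if exit is selective, which the article does not show.

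**Conclusion.** The point holds for costs, QALYs and the cost-effectiveness ratios. The article itself fixes a population that depends on surviving and staying insured to t24, so those results describe only such people, whatever the exit rates. Whether the between-group difference is biased, and in which direction, cannot be determined from the article: it depends on exit, or its link to outcome, differing by group. On the assumptions shown, 14–70 of 700 per arm are dropped at 2–10% exit, and 0–0.014 QALY per person is omitted for a mortality difference of 0–2 percentage points at utility 0.7 with one year lost per death. The existence of the rule is certain; material bias is possible, not demonstrated. For time to surgery, the wording needs clarifying, and no error is established.

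**What to change.** - Require continuous membership only from tm24 to t0, as Table 1 already does, and analyse all matched participants from t0.
- For deaths, count costs to the date of death and utility zero afterwards.
- For a change of insurer, treat the remaining interval as censored or missing, using inverse-probability-of-censoring weights or multiple imputation.
- Keep the set insured through t24 as a sensitivity analysis. Comparing the two shows how far a mortality difference, possibly residual confounding, drives the result.
- State that the membership rule does not apply to time to surgery, and censor there at exit or death.

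The cost is a change of analysis wording, modest extra programming, and reliance on a censoring or imputation model for those who leave. It needs dates of exit and death, which the article does not say are available; this should be confirmed with the insurer. No additional questionnaire or follow-up visit is required.
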